### Study design and population

MANTRA is a prospective, multi-arm, global, post-marketing study with long-term follow-up planned through to 10 years. Review and approval by a certified local ethical committee or institutional review board is needed for the master protocol and substudy protocol(s) as per local regulations. All subjects are required to provide informed consent before undergoing any clinical investigation-specific assessments (e.g. quality of life) and treatments.

The plan is to enroll approximately 2150 subjects in around 130 sites worldwide over 4 years, (1650 in the aortic substudy, 300 in the mitral/tricuspid and 200 in the MEMO 4D substudy) with follow-up visits scheduled at the time of hospital discharge, at 30 days after the procedure, and then annually up to 10 years (Figs. 2 and 3). Participants diagnosed with heart valve disease who are suitable to undergo valve replacement with a Corcym device per the approved instructions for use and who are willing to comply with the follow-up schedule can be included. Subjects participating in another clinical investigation that could confound the results of the MANTRA study and those with a life expectancy ≤ 12 months will be excluded. Subjects less than 18 years of age, pregnant or breastfeeding women, and other vulnerable populations (e.g. children, or subjects unable to sign informed consent or persons unlikely to be able to comply with follow-up) are not planned to be enrolled. In addition, long-term data obtained from participants treated with either the Perceval Plus™ device or treated with the Bicarbon™ prosthetic valve family and followed under a low international normalized ratio regimen from the SURE-AVR study (NCT02679404), will be transferred into the aortic substudy database.

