### Endpoints

The primary endpoint is device success, adapted from the Valve Academic Research Consortium (VARC-3) [3] and from the Mitral Valve Academic Research Consortium (MVARC) guidelines [4] for the aortic substudy and for the mitral/tricuspid and MEMO 4D substudies, respectively. These two guidelines were developed by expert panels in an effort to provide guidance on the appropriate selection of clinical endpoints and definitions to increase consistency in the evaluation and reporting of trial outcomes. Secondary endpoints include mortality, morbidity, hemodynamics, procedural information (e.g. surgical times), intensive care unit management, and patient-related outcomes (e.g. New York Heart Association [NYHA] and quality-of-life improvement). Importantly, the definitions of complications, valve/ring degeneration for safety endpoints are aligned with the current VARC and MVARC guidelines to ensure homogenous reporting, adjudication, and comparison between devices and therapeutic strategies. Furthermore, the study will analyze patient related outcome endpoints, not only related to improvement of the NYHA class, but also considering the improvement of Quality of Life (Kansas City Cardiomyopathy Questionnaire, KCCQ-12) integrated with survival, as suggested by VARC-3 guidelines. Hemodynamic and structural performance from site-reported echocardiography findings, intra-operatively, discharge, at 30 days (+ 14 days), at 12 months after implant and at each subsequent follow-up collected as per the recommendations for the imaging assessment of prosthetic heart valves [5] will be analyzed according to the different device indications. The full list of study endpoints is detailed in Table 2.

**Table 2 Tab2:** Aortic, Mitral/tricuspid, and MEMO 4D substudy endpoints

	Aortic substudy (n = 1650)	Mitral/tricuspid substudy (n = 300)	MEMO 4D substudy (n = 200)

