Primary endpoint	Device success at 30 days (+ 14 days) adapted from VARC-3 guidelines: Technical success Freedom from mortality Freedom from surgery or intervention related to the device or to a major vascular or access-related or cardiac structural complication Intended performance of the valve (mean gradient < 20 mmHg and less than moderate aortic regurgitation)	Device success at 30 days (+ 14 days), adapted from MVARC guidelines: Procedural mortality or stroke; AND Proper placement and positioning of the device; AND Freedom from unplanned surgical or interventional procedures related to the device or access procedure; AND Continued intended safety and performance of the device	Device success at 30 days (+ 14 days), adapted from MVARC guidelines: Procedural mortality or stroke; AND Proper placement and positioning of the device; AND Freedom from unplanned surgical or interventional procedures related to the device or access procedure; AND Continued intended safety and performance of the device
Secondary endpoints	Safety and performance assessments at 30 days, 12 months, and annually after implant Collection of procedural and hospitalization information Patient outcomes	Safety and performance assessments at 30 days, 12 months, and annually after implant Collection of procedural and hospitalization information Patient outcomes	Safety and performance assessments at 30 days, 12 months, and annually after implant Collection of procedural and hospitalization information Patient outcomes

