### Statistical analysis

Given the non-confirmative nature of the aortic and mitral/tricuspid substudies, neither formal sample size calculations nor formal hypothesis testing will be conducted. In contrast, a sample size calculation was performed for the MEMO 4D substudy, with the endpoint defined as restoration of annular height commissural width ratio (AHCWR) at end-diastole and end-systole at 12 months (± 30 days) after implantation compared with values measured at baseline (improvement versus baseline in AHCWR at post-implant time points indicates that the valve is functioning properly). The sample size calculation was performed only for saddle-shaped size MEMO 4D mitral annuloplasty rings, using the *t-*test for paired means (i.e. before and after device implant) and the following parameters: 90% power, 1-sided 5% significance level, standard deviation of 8 and mean of 5% (assuming a baseline AHCWR of 15% and a postoperative value of 20% at 12 months). AHCWR values range from 20 to 30% when a mitral valve functions properly and from 10 to 17% for diseased valve [8–12]. The sample size calculated using the above parameters was 41 for MEMO 4D featuring a saddle-shape configuration (34−42 mm). The total study sample was 200 and it is projected that at least 60 participants will be treated with MEMO 4D saddle-shape configurated rings, therefore meeting the sample size requirement for the hypothesis testing.

The number and percentage of subjects with device success at 30 days according to the VARC-3 [3] and the MVARC [4] guidelines, along with each individual component, will be presented. According to their statistical distribution, continuous variables will be presented either as means (± standard deviations), minimum and maximum values, or median with interquartile ranges. Categorical variables will be presented as numbers and percentages.

Survival analyses will be conducted to analyze time-to-event variables. Participants without events will be censored at their last known event-free time point. Survival curves will be constructed using Kaplan–Meier estimates; the number of subjects at risk, of censored subjects, of events, and the event-free survival rate and 95% confidence intervals of the survival rate for each time interval will be presented in a summary table.

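### Kaplan-Meier with one censoring rule and no exception for death would, read literally, overstate the 10-year risk of non-fatal events that patients actually face

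*Protocol article*

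**What the plan says.** The Statistical analysis section of the protocol article treats all time-to-event outcomes together: "Survival analyses will be conducted to analyze time-to-event variables". The censoring rule follows: "Participants without events will be censored at their last known event-free time point". The estimator is fixed: "Survival curves will be constructed using Kaplan–Meier estimates". The reported result is the "event-free survival rate and 95% confidence intervals of the survival rate for each time interval will be presented in a summary table". Death is not mentioned in this rule, and no cumulative-incidence or competing-risk estimate appears anywhere in the article.

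The Endpoints section shows that fatal and non-fatal outcomes are both in scope: "Secondary endpoints include mortality, morbidity, hemodynamics". It adds that "the definitions of complications, valve/ring degeneration for safety endpoints are aligned with the current VARC and MVARC guidelines". Table 2 has safety and performance assessed at 30 days, 12 months and annually, and Study design and population describes "long-term follow-up planned through to 10 years". The Discussion says that a master SAP and substudy SAPs exist; they are not available here.

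**The concern.** Someone who dies without the event can no longer have it. If that death is handled as ordinary censoring, Kaplan-Meier in effect lets the participants still under observation stand in for the dead. One minus the curve then estimates the risk in a population in which nobody dies, not the proportion of treated patients who will experience the event.

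The gap widens with follow-up and with mortality, so it falls on the late results, and long-term outcomes in routine practice are what the article says the study will provide. The aortic and mitral/tricuspid substudies (1650 + 300 = 1950 of 2150 planned participants) have no formal hypothesis tests, so descriptive estimates are their main product. A 10-year degeneration or complication risk that is too high could be quoted to patients and regulators as the risk patients face.

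**Working it through.** **Step 1: what the rule does to a death.** The rule censors every participant without the event. Someone who dies free of degeneration is a participant without that event. No exception is written, so under the literal rule that person is censored at or before death.

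**Step 2: direction.** Whenever some participants die event-free and events occur afterwards, 1 minus Kaplan-Meier with deaths censored is larger than the cumulative incidence. This needs no assumption about rates.

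**Step 3: size.** The article states no event rate, mortality rate or long-term risk, so there is no figure of its own to reproduce. Every rate below is an assumption; only the 10-year horizon comes from the article. Take constant, independent hazards h_e (event) and h_d (death):

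- deaths censored: 1 − KM(10) = 1 − exp(−10·h_e)
- death as a competing event: CIF(10) = h_e/(h_e + h_d) × [1 − exp(−10·(h_e + h_d))]
- 10-year mortality: 1 − exp(−10·h_d)

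For h_e = 0.01, 1 − KM = 1 − exp(−0.1) = 0.09516. For h_d = 0.03, CIF = 0.25 × (1 − exp(−0.4)) = 0.25 × 0.32968 = 0.08242, and 0.09516/0.08242 = 1.155. The other rows follow in the same way.

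| h_e per year | h_d per year | 10-year mortality | 1 − KM | CIF | Ratio |
|---|---|---|---|---|---|
| 1% | 3% | 26% | 9.5% | 8.2% | 1.15 |
| 1% | 5% | 39% | 9.5% | 7.5% | 1.27 |
| 1% | 7% | 50% | 9.5% | 6.9% | 1.38 |
| 2% | 5% | 39% | 18.1% | 14.4% | 1.26 |

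At a 1% per year event hazard the absolute excess is therefore between 9.5 − 8.2 = 1.3 and 9.5 − 6.9 = 2.6 percentage points.

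**Step 4: sensitivity to the shape of the event hazard.** Degeneration may come late. Fix 1 − KM at 10% at 10 years and vary 10-year mortality from 20% to 60%. With a constant event hazard, the CIF falls from 9.0% to 6.6% (ratios 1.11 to 1.52). With a rising event hazard (Weibull, shape 2.5, integrated numerically), it falls from 8.6% to 5.3% (ratios 1.17 to 1.87).

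**Step 5: early time points.** At 1 year, with 1 − KM of 2% and mortality of 3% or 5%, the CIF is 1.97% or 1.95%, so the ratio is 1.015 or 1.026. The effect is negligible there.

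**Step 6: what is untouched.** Device success at 30 days is reported as a number and percentage. For all-cause mortality, death is the event itself. The MEMO 4D hypothesis is a paired comparison of annular height commissural width ratio at 12 months. None of these depends on the censoring rule for non-fatal events.

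**The case against.** **The handling of death is inferred.** The table is to show an event-free survival rate, which could mean alive and event-free. If death counts as an event, this bias does not arise. That stands as a limit: the article never says in so many words that deaths are censored. But nor does it say that death counts as an event, and a composite of that kind would give no event-specific risk of degeneration. Either way, the handling of death needs to be stated.

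**The SAPs may deal with it.** They may. If the article were merely silent on the estimator, there would be no point to raise. Here it states a general estimator and censoring rule without exception; if the SAPs differ, the texts need aligning.

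**Kaplan-Meier answers a legitimate question.** For device durability, risk with death removed is a defensible target, provided that death and the event are independent. That stands too: Kaplan-Meier alone is incomplete for patient risk rather than worthless, which is why both estimates should be shown.

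**Stronger readings that the documents do not support.** A reader might infer that the rule distorts comparisons between device families. The table in the working shows otherwise under its own model: with the event hazard held at 1% per year, Kaplan-Meier gives 9.5% at every mortality level, and it is the cumulative incidence that moves. The article also gives no age or mortality profile by device that would support such a claim. A reader might also extend the point to a long list of events. The article names morbidity, complications and valve/ring degeneration in broad terms. Stroke appears only within the 30-day mitral/tricuspid and MEMO 4D composites. Device-related reintervention likewise appears only in the 30-day composites, as in the aortic item "Freedom from surgery or intervention related to the device". Nowhere does the article list which secondary endpoints are time-to-event variables.

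**Conclusion.** The point holds for non-fatal long-term endpoints under the literal reading of the stated rule: 1 minus Kaplan-Meier would overstate the risk that patients actually face. The direction is certain under that reading; the size is not known from the article. For a 1% per year event hazard and 3% to 7% per year mortality, with constant and independent hazards, the relative excess at 10 years is about 15% to 38%. It would be larger if events cluster late or mortality is higher.

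This is a correction worth making, but not a critical one. It touches neither a primary endpoint nor the one hypothesis test described, the error is towards overstating harm, and no additional data are needed to put it right.

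**What to change.** - State that death is a competing event for non-fatal time-to-event endpoints, and list which endpoints these are.
- For those endpoints, report the cumulative incidence function (Aalen-Johansen) with 95% confidence intervals as the estimate of patient risk.
- Keep Kaplan-Meier for all-cause mortality and for composites that include death, and say explicitly when event-free survival counts death as an event.
- Show Kaplan-Meier freedom-from-event figures alongside, labelled as risk with death removed, for device durability and for comparison with older literature.
- Where devices are contrasted, add cause-specific hazards, because cumulative incidence itself depends on mortality.

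The cost is wording in the protocol and SAPs plus standard software output; mortality and serious adverse events are already being collected. The small downside is two sets of figures to report and explain. Enrollment was still ongoing when the article was written, so the change can precede the long-term results.

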### Current status of the study

The study was activated in 2021, with the first subject enrolled on July 1, 2021. Forty-four centers have been activated to date, including sites in Europe, North America and Canada, and South Korea. Currently, 393 participants have been enrolled, and follow-up data from 93 participants in the SURE-AVR study have been transferred. Sixty-six of them belong to the Bicarbon™ low international normalized ratio subgroup and twenty-seven to the Perceval Plus™ subgroup. Thirty additional centers are in the process of being activated.

## Discussion

To our knowledge, MANTRA is the first study in the medical device arena to adopt the “umbrella” master-protocol concept. This concept provides a solution to gathering long-term prospective information on the entire Corcym cardiac surgery portfolio products for the treatment of heart valve diseases within a unified trial structure. Accordingly, the original master-protocol concept, developed to provide solutions for complex disease treatments such as oncology, was modified for efficient and economic data collection in the heart valve disease area. There are several advantages to this approach. First, instead of setting up individual studies for each device, a single study program is needed. Second, since many of the participating investigators and sites are using more than one product from the Corcym portfolio and can participate in more than one substudy, a single master-protocol reduces time, resources, and costs for both contract set-up and submissions to ethical committees and institutional review boards. Third, study management and oversight, including data management, monitoring, and data analysis, can be managed by a single team. Having one common database ensure more consistent data return for all the devices with more efficient access for data analysis. Moreover, the data are linked to the company’s quality system, ensuring that valve-related serious adverse events are notified in real time to the vigilance reporting system, ensuring compliance with regulatory requirements in the post-marketing setting.

Further advantages are foreseen for data analysis from the MANTRA study: the Statistical Analysis Plan (SAP) has also adopted the umbrella structure, and a master SAP and substudy SAPs have been created. Having all the data in a single database facilitates the prospective analysis of product families with devices that may be used in more than one indication, with clinical oversight of the experts in the Steering Committee. The structure and broad data output will generate valuable information for submission to regulatory bodies and will support publications and dissemination to the medical community and to the participating institutions, deepening the knowledge on company devices and strengthening the evidence on specific uses. Indeed, the long-term prospective and multicentric information collected in the study, which include safety, performance, and patient related outcomes, will provide clinical evidence to ensure the best treatment option are provided to the patients. On this regard, the data collection in MANTRA includes parameters needed to evaluate the effect of adoption of Enhanced Recovery After Surgery (ERAS) protocols in cardiac surgery. The study can provide information on integration of ERAS to valve surgery (especially in sutureless valve and advanced rings for repair) that could transform it from limited access surgery on to a more “physiological” surgery. This could increase clinical benefits and further improve patient outcomes, especially in high-risk populations needing additional support. We believe that the concept of minimally invasive surgery can evolve even further by going beyond a simple reduction of the surgical incision: by increasing the technical and technological content of the intervention according to a multidisciplinary approach, clinical outcomes after minimally invasive surgery can be enhanced, and postoperative recovery may be fastened with an increased patient and family satisfaction [13, 14].

Furthermore, leveraging on its adaptive design, the MANTRA study may support product development, with the possibility to include ad-hoc substudies and/or study related endpoints to support multiple claims or different indications on old or new products, whenever they become commercially available.

Clearly this concept needs extra efforts in terms of its set-up. Whereas the different treatment areas, albeit all within heart valve disease, show variation in terms of data collection needs and treatment options, they all have to be addressed within the database setup and in the SAP. The Steering Committee has provided extensive input to help refine the data collection. Furthermore, working within a global environment, local expertise is needed to ensure regulatory compliance and diligence, which was solved by contracting with local consultants, who are supporting sites across the globe to obtain approvals and to perform data monitoring. Extra care was taken to review the local national requirements even though the study follows standard-of-care.

Final conclusions on the cost-effectiveness of this approach cannot be drawn at this stage. However, as sites can enroll in one or more substudies, it is assumed that the greatest cost−benefit will be related to start-up costs. For example, if a site participates in all three substudies, start-up costs and ethical review costs apply only once, reducing the total number of administrative procedures that need to be activated. In addition, there should also be a saving in resources, as traditionally these three substudies would have been organized as individual studies, with all study costs multiplied threefold. A further important cost-saver is the costs for development and maintenance of the database. Together, these factors are likely to translate into benefits that will become more evident over time.

## Data Availability

Not applicable.

## Abbreviations

SAP: Statistical analysis plan
CRF: Case report form
VARC: Valve academic research consortium
MVARC: Mitral valve academic research consortium
NYHA: New York heart association
KCCQ: Kansas City cardiomyopathy questionnaire
EQ-5D-5L: 5-Level EQ-5D questionnaire
AHCWR: Annular height commissural width ratio
ERAS: Enhanced recovery after surgery
ICU: Intensive care unit
QoL: Quality of life
TEE: Transesophageal echocardiography
TTE: Transthoracic echocardiography
